### Data collection

A.Medical records and direct data collection

Clinical data were gathered from medical records and databases by qualified reviewers. A data collection form and instruction manual were developed to guide the data collection process to ensure consistency among centers and reviewers.

Upon hospital admission, baseline data were collected that included information on patient sociodemographics, clinical data (including data from the initial diagnosis, the pre-intervention process, onset of symptoms, habits and lifestyles (physical activities, alcohol intake or smoking habit), personal and family background, general comorbidity data as recorded in the Charlson Comorbidity Index [16], bowel-specific comorbidities, diagnostic and screening tests, pre-intervention treatments, and duration between relevant time points in the diagnostic process), preoperative data [including analytical, tumor markers, diagnostic tests and pre-intervention clinical staging (pre-TNM), and tumor site], data from the outpatient anesthesia visit prior to surgical intervention (ASA stage [17], physiological and cardio-respiratory parameters and tests, and consciousness level based on the Glasgow scale [18]). Variables from the different versions of the POSSUM were specifically included to test all those rules.

### Data related to hospital admission

Data on the surgical intervention (including type of intervention, surgical severity, aggravate diagnosis, type of anesthesia, antibiotic prophylaxis, surgical approach, type of surgery, invasion of adjacent organs, additional surgical procedures associated to local extension of the disease, intra surgical complications, complication grade, duration of surgery, and other information specific to the colon- or recto-surgical intervention), and Intensive Care Unit (ICU) period information (duration, mechanical ventilation requirements, parenteral nutrition, antibiotics, presence of complications, and death).Anatomical pathology data, including tumor-free margin, histologic diagnosis, pre-TNM (pTNM), lymph nodes analyzed and affected, degree of tumor differentiation, invasion, remission, and biological markers.

In relation to the biological marker objective of the study, 800 paraffin-embedded samples were collected for immunohistochemical analysis to identify clinical and pathological features associated with changes proliferation, apoptosis and angiogenesis, and the role of these changes in the occurrence of adverse results such as cancer relapse and mortality. Samples were collected from patients attending the following hospitals: Hospital de Antequera, Hospital Costa del Sol, Hospital de Valme, Hospital Virgen del Rocío, Hospital Virgen de las Nieves, Hospital Galdakao-Usansolo, and Hospital Basurto.c.Other data related to hospital admission (length of stay, presence and degree of complications, treatment information, need for reintervention, or death). Complications were grouped in the following categories: surgical, medical, infectious, and hematological (hemorrhage/thrombosis/embolism) (see Additional file 1: Table S1).

Data were subsequently collected up to 30 days after surgery (analytics, diagnostic tests, presence of complications, readmissions, reintervention, social service requirements, or death). Oncologic treatment information is shown in the adittional files section as Table 2.

**Table 2 Tab2:** Basic description of the whole sample at baseline

	*N* (%)	Main cancer location	
		Rectal	Colon
Total	2749	770 (28.01)	1979 (71.99)
Gender (Men)	1749 (63.62)	522 (67.79)	1227 (62.00)
Age^a^	68.50 (10.97)	67.14 (11.26)	69.02 (10.81)
Charlson Comorbidity index^a^	2.88 (1.29)	2.83 (1.22)	2.90 (1.32)
ASA index			
I,II	1548 (57.92)	450 (59.92)	1098 (57.13)
III	1020 (38.16)	277 (36.88)	743 (38.66)
IV	105 (3.93)	24 (3.20)	81 (4.21)
Surgical approach (main)			
Open surgery	1139 (41.89)	307 (40.55)	832 (42.41)
Laparoscopy	1580 (58.11)	450 (59.45)	1130 (57.59)
Laterality of the tumor (Right –transverse side)	834 (42.14)	NA	834 (42.14)
pTNM			
0, I, II	1581 (57.85)	485 (63.32)	1096 (55.72)
III	892 (32.64)	221 (28.85)	671 (34.11)
IV	260 (9.51)	60 (7.83)	200 (10.17)

Laterality of the tumor: Right-transverse side (appendix, cecum, ascending colon, right hepatic flexure and transverse) versus left side (left splenic flexure, descending colon, and sigmoid colon)

*ASA*, American Society of Anesthesiologists

*pTNM* pathological tumor-node-metastasis staging

^a^Means and, in brackets, standard deviation

Information was next collected through the first year of follow-up, including need for and type of treatment (separately evaluated for colon or rectal tumors), radiation therapy, chemotherapy (treatment schedule, neo or adjuvant therapy, number of cycles, presence and degree of treatment complications, and supportive care requirements), other medical treatments and psychological support. Information was also collected on laboratory and diagnostic tests performed, presence of complications, additional surgeries, tumor recurrence, readmission or reintervention, and death.

Information collected at the 2-, 3- and 5-year visits was similar to that of the 1-year visit.B.Patient reported outcomes measures (PROMs)

Patients completed the following questionnaires prior to surgery and in the follow up after surgery: EuroQol-5D (EQ-5D), EORTC QLQ-C30 (The European Organization for Research and Treatment of Cancer Quality of Life Questionnaire-C30) and QLQ-CR29 (European Organization for Research and Treatment of Cancer Questionnaire Module for Colorectal Cancer), the Duke-UNC Functional Social Support Questionnaire (FSSQ), the Hospital Anxiety and Depression Scale (HADS), and the activities of daily living (ADL) Barthel Index (BI).

The EQ-5D is a generic health-related quality of life (HRQoL) questionnaire which consists of two parts, the first of which is a description of the state of health in five dimensions: mobility, self-care, usual activities, pain/discomfort and anxiety/depression. Each of these dimensions is measured by three answer options that define different levels of severity. The second part is a visual analogue scale in which patients rate their health on a scale displayed in the form of a thermometer (20 mm), whose ends are 0 (worst imaginable health state) to 100 (best state imaginable health) [19]. This questionnaire has been translated into and validated in Spanish [20].

The EORTC QLQ-C30 is a HRQoL questionnaire for evaluating the for cancer patients undergoing treatment, and has shown good validity and reliability in its Spanish adaptation (Cronbach’s alpha coefficient of 0.7). It consists of 30 items, 28 of which have four possible answers (not at all, a little, quite a bit, very much) and two items with seven response options (a visual analogue scale where one is “very poor” and seven “excellent”) [21, 22]. The timeframe assessed refers to the previous week. The scores on each scale are transformed so that the final values are between 0 and 100. In addition to this overall score, the instrument consists of three scales: Global health status, in which a high score represents a high performance in terms of overall health; Functional–scale, which consists of five subscales of operation: physical, role, emotional, cognitive and social; and a Symptoms scale, describing a number of symptoms: fatigue, nausea, vomiting, pain, dyspnea, insomnia, decreased appetite, constipation, diarrhea and financial difficulties. A high score on each of these scales represents a high level of symptoms or problems in the patient. The QLQ-CR29 questionnaire was developed following revision of the QLQ-CR38, and has been demonstrated internationally to have both sufficient validity and reliability to support its use as a supplement to the EORTC QLQ-C30 for assessing patient-reported outcomes during treatment for colorectal cancer in clinical trials and other settings. The QLQ-CR29 questionnaire contains 29 items, 18 of which address gastrointestinal symptoms, pain and problems with micturition, and separate scales are available for participants with or without a stoma, while separate items address sexual function in men or women. The response categories for each item are the same as those used in the QLQ-C30. This questionnaire has also been validated in Spain [23, 24].

The HADS questionnaire is designed specifically for individuals with a physical illness. It is divided into two subscales, with seven questions pertaining to symptoms associated with anxiety and seven with depression. Each of the 14 items consists of a 4-point Likert scale (ranging from 0 to 3) that applies to the previous week. A total score for each subscale is then calculated, ranging from 0 to 21 [25]. The HADS has been translated into and validated in Spanish [26].

The Duke-UNC FSSQ questionnaire is composed of 11 items, each of which is rated on a five-point Likert scale ranging from 1 to 5: the higher the score, the better the perceived social support. It assesses subjective social support in two domains, Confidant support: 6 items (score range 6–30) and Affective support: 5 items (score range 5–25), and provides an overall social support measure (score range: 11–55) [27]. The questionnaire has been translated into and validated in Spanish [28].

The BI questionnaire consists of 10 items that assess the ability to perform certain basic activities of daily life without help. It includes 2- and 4-point response options that produce a score ranging from 0 (completely dependent) to 100 (completely independent), with intervals of 5 points [29]. The BI has been translated into and validated in Spanish [30].

Patients were first contacted upon inclusion in the surgical waiting list for a surgical intervention or were interviewed during their hospital admission period. Questionnaires were subsequently provided at 30 days, and at 1, 2, 3 and 5 years after surgery. In all instances, a reminder letter was sent to patients who had not replied after 15 days. Those who had not responded after a further 15 days received another reminder letter and, where feasible, contacted by telephone.

Questionnaires for the 30 day follow up visit were sent to patients attending the following hospitals: Hospital Costa del Sol, Hospital Valme, Hospital Virgen del Rocío, Hospital Virgen de las Nieves, Corporació Sanitaria Parc Taulí, Hospital Universitario La Paz, Hospital Infanta Sofía, Hospital Clínico San Carlos, Hospital Fundación Alcorcón, Hospital Basurto, Hospital Cruces, Hospital Donostia, Hospital Galdakao-Usansolo, Hospital Txagorritxu.

Figure 3 illustrates the data gathering process established for the entire follow-up period.

### Safety considerations

There is no explicit intervention in this study. Nevertheless, due to the sensitive nature of the disease and for reasons of confidentiality, all information provided to patients, either directly by the researchers or reviewers or included in the questionnaires, avoid references to cancer or tumors, referring instead, to “your bowel problem”. Patients may refuse to participate at any time during the study, whether during recruitment or follow-up. Furthermore, patients who prefer to complete the questionnaire by phone are permitted to do so. All participating centers have referring staff available for questions that the patient or patient’s family may have about the research project.

### Follow-up

Follow-up visits up to two years will be performed at all 22 participating hospitals. Due to financial restrictions and organizational resources, 3- and 5-year follow-up visits will be restricted to 18 hospitals (Hospital de Antequera, Hospital Costa del Sol, Hospital Universitario de Valme, Hospital Universitario Virgen del Rocío, Hospital Universitario Virgen de las Nieves, Hospital Universitario de Canarias, Corporació Sanitaria Parc Taulí, Hospital del Mar, Hospital Clínico San Carlos, Hospital Universitario La Paz, Hospital Infanta Sofía, Hospital Universitario Fundación Alcorcón, Hospital Galdakao-Usansolo, Hospital Universitario Araba, Hospital Universitario Basurto, Hospital Universitario Cruces, Hospital Hospitalario Donostia, and Hospital Universitario Doctor Peset).

### Data management and statistical analysis

A.Sample size selection

Studies of predictive model development indicate that is necessary to include at least 10 events of the dependent variable of interest (in this case: mortality, major complications, relapses or readmissions) for each independent variable included in the multivariate logistic regression model [31, 32]. Therefore, we estimated that at least 100 events of the dependent variable in the sample are required in order to ensure that the regression model would adequately converge. Previous data indicate that the number of events of the dependent variable mortality would be > 15 % of patients operated on in the first year, higher that the expected percentages of other parameters. We therefore estimated that more than 300 events of any of the dependent variables of interest should be included.

Sampling: we consecutively collected all new cases until the sample size was achieved.B.Missing data assumptions and recoding of variables

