Predictive models will be developed to address objectives 1 and 2. The overall sample will be randomly divided into derivation and validation sets. On the one hand, for binary outcomes (such as death, tumor recurrence, major complications, or readmission), multivariate hierarchical logistic models will be used. Goodness-of-fit of models will be assessed by means of the Hosmer–Lemeshow test (*p*-values > 0.05 indicate good model calibration) and the area under the Receiver Operating Curve (ROC), AUC, will be used to evaluate the discrimination ability of the final performance models. An AUC value > 0.80 will indicate that the model discriminates well. Furthermore, multivariate Cox regression models will be used to answer to those objectives. On the other hand, in cases of continuous outcomes (variables related to deterioration of quality of life) as with objective 3, the use of multivariate hierarchical linear mixed models is proposed. The intraclass correlation coefficient (ICC) will be calculated to assess the correlation among observations within a cluster by dividing the patient variance by the total sample variance. A small coefficient would indicate that patients and participant centers are independent.

For study endpoints related to health services research, the following statistical approaches will be used: for two-level outcomes, the Student’s t-distribution or the non-parametric Wilcoxon test (for non-normal distributions) will be applied. Where there are three or more categories in the outcome, ANOVA analysis or a Kruskal–Wallis approach (for non-normal distribution) are the proposed tests. Otherwise, for categorical variables, the Chi-square test (or Fisher’s Exact method, where required) will be used. Multivariate models will be used as needed for appropriate adjustments. For some analyses, subgroups based on tumor location (colon or rectum) will be identified.

An analysis of comparative costs between two alternative surgical approaches (open and laparoscopic surgery) will be performed. For this purpose, generalized linear models (GLM) will be employed using the patient level cost as the dependent variable and taking clinical covariates into account (age, sex, stage, among others). The statistical model will determine which covariates are associated with higher costs, as well as any significant differences in cost between the two alternatives. Analysis will be conducted at 2 and 5 years of follow up.

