## Discussion

As illustrated in Fig. 2, by the time of manuscript preparation, 2749 patients had been recruited according to the study protocol described previously, 1980 of which had been diagnosed with colon cancer and 769 with rectal cancer. This population represents a relatively large cohort of colorectal cancer patients for prospective follow up. Description of the basic characteristics of the sample, stratified by colon or rectal cancer diagnosis, is displayed in Table 2.

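### The 100-event floor is justified by convergence and counts variables in the model over the whole sample, so it does not protect the prediction rules from overfitting in the derivation set

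*Protocol article*

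**What the plan says.** In the Protocol article, Data management and statistical analysis, part A (Sample size selection), the rule is that it "is necessary to include at least 10 events of the dependent variable of interest" "for each independent variable included in the multivariate logistic regression model". From this the plan derives its minimum: "at least 100 events of the dependent variable in the sample are required in order to ensure that the regression model would adequately converge". It does not state how many variables are meant.

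The same paragraph then puts first-year mortality above 15% "of patients operated on in the first year, higher that the expected percentages of other parameters", and concludes that "more than 300 events of any of the dependent variables of interest should be included".

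Part C (Statistical Analysis) says that for binary outcomes "multivariate hierarchical logistic models will be used", after a random division of the whole sample into derivation and validation sets. No split ratio is given. Performance is to be judged by the Hosmer–Lemeshow test and the AUC. The Discussion reports that "2749 patients had been recruited according to the study protocol".

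The sections Data collection and Data related to hospital admission list several dozen items and groups of items. They do not say which are candidates for any particular model.

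**The concern.** The stated rule has three weaknesses.

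- **Criterion.** Convergence only means that the fitting algorithm reached a solution. The article promises clinical prediction rules for everyday use, which need predicted risks that hold in new patients.
- **What is counted.** Overfitting depends on every parameter tried against the outcome, including each category level and nonlinear term. A rule worded for variables included in the model does not clearly limit that number.
- **Where events are counted.** The floor refers to the whole sample, but the random split implies that models are fitted in the derivation part only.

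If a model is overfitted, its predictions are too extreme: high risks are overstated and low risks understated. It also looks more discriminating in the derivation data than it is elsewhere.

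**Working it through.** **Inputs from the article:** 10 events per variable; floor of 100 events; expectation of more than 300 events; first-year mortality above 15%; 2749 patients recruited.

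**Assumptions:** derivation share of one half to two thirds; 40 to 50 candidate parameters. By a rough reading, Data collection lists about 20 to 25 items plus the POSSUM variables, and Data related to hospital admission about 30.

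**1. The plan's own figures.** 100 / 10 = 10 variables, so the floor is reproduced only if 10 variables are meant. The 300 events correspond to 300 / 10 = 30 variables, and at 15% to 300 / 0.15 = 2000 patients. With 2749 patients, 0.15 × 2749 = 412 first-year deaths. For mortality, the expectation of more than 300 is therefore consistent.

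**2. Effect of the split.** 100 × 1/2 = 50 events (5 parameters at 10 each) and 100 × 2/3 = 66.7 events (6.7 parameters). Likewise 300 becomes 150 to 200, and 412 becomes 206 to 275.

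**3. Less frequent outcomes.** 300 / 2749 = 10.9%. An outcome at 10% gives 275 events and one at 5% gives 137. That 300 is reached by the most frequent outcome does not show that the others reach it.

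**4. Events per candidate parameter.**

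| Events in whole sample | 40 candidates | 50 candidates | Derivation set, 40 to 50 candidates |
|---|---|---|---|
| 100 | 2.5 | 2.0 | 1.0 to 1.7 |
| 300 | 7.5 | 6.0 | 3.0 to 5.0 |
| 412 | 10.3 | 8.2 | 4.1 to 6.9 |

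For the 300 row, the derivation range runs from 150 / 50 = 3.0 to 200 / 40 = 5.0.

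**5. Expected shrinkage by formula.** S = 1 − P / LR, with LR = −n ln(1 − R²), where R² is the Cox–Snell value. At a 15% event rate its maximum is 0.571. Nagelkerke R² of 0.15 to 0.35 is assumed, so R² = 0.0856 to 0.200. For P = 50 and n = 2000 (300 events), LR = 179 to 446, giving S = 1 − 50/179 = 0.72 to 1 − 50/446 = 0.89. The same formula gives:

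| Patients (events at 15%) | S, P = 50 | S, P = 10 |
|---|---|---|
| 667 (100) | 0.16 to 0.66 | 0.83 to 0.93 |
| 1374 (206) | 0.59 to 0.84 | 0.92 to 0.97 |
| 2000 (300) | 0.72 to 0.89 | 0.94 to 0.98 |
| 2749 (412) | 0.80 to 0.92 | 0.96 to 0.98 |

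**6. Simulation.** Logistic models with backward selection at p < 0.05, 15% event rate, 8 true predictors with log-odds ratios from 0.45 to 0.15, independent normal predictors, and a test set of 20,000. Selection method and effect sizes are assumptions. Where two figures stand, they come from two separate runs.

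| Candidates | Events used for fitting | Calibration slope in new patients |
|---|---|---|
| 10 | 100 | 0.83 |
| 40 | 100 | 0.71 to 0.74 |
| 40 | 150 | 0.81 |
| 40 | 206 | 0.86 |
| 40 | 300 | 0.87 to 0.90 |
| 40 | 412 | 0.91 to 0.92 |

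A slope of 1 means no overfitting. With 40 candidates and 100 events, the AUC was 0.746 in the derivation data and 0.695 in new patients. The first row matters for the remedy: exactly 10 events per candidate still gave a slope of only 0.83. Uniform shrinkage of the full 40-candidate model raised the slope to 0.93 to 0.98.

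**The case against.** The strongest reply is that the study is not sized at 100 events. That is a floor; two sentences later the plan expects more than 300, and the recruited cohort implies about 412 first-year deaths. At 300 or more fitting events the simulated slopes are 0.87 or better, even with 40 candidates. This stands, so a reader should not infer that the models rest on 100 events. It does not rescue the rule, because the 300 is supported by mortality alone and is also counted before the split.

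A reader might further infer that the rule counts only variables surviving selection, that some 50 candidates will be screened, or that the models will certainly be overfitted. The article supports none of these. The word used is included, which may mean all variables entered, and no selection procedure is stated. The lists describe what is collected for five objectives, and some of it is reduced: symptoms gain a single any/none indicator and surgical severity has three levels. The POSSUM variables were collected to test existing scores ("Variables from the different versions of the POSSUM were specifically included to test all those rules"), which does not make them candidates for new models.

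Finally, candidate lists, selection and shrinkage may be in a fuller plan, and their absence here is no fault. The validation set and the commitment to TRIPOD are real safeguards. A validation set can reveal overfitting but does not prevent it, and the stated rule and its rationale would still need correcting.

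**Conclusion.** The point holds as a flaw in a stated rule. The floor of 100 events corresponds to 10 parameters in the whole sample and about 5 to 7 in a derivation set of one half to two thirds. Convergence does not guard against overfitting. The expectation of more than 300 events eases the problem for mortality but is not shown for any outcome below 10.9%.

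If 40 to 50 parameters are screened, 300 events leave about 3 to 5 per candidate for fitting. The models are then at risk of overfitting, with a simulated slope of about 0.81 at 150 fitting events and 0.87 to 0.90 at 300. The size depends on the assumed candidate number, split ratio, predictor strength and selection method. With about 10 candidates and 300 or more fitting events the risk is small (expected shrinkage 0.94 or higher).

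**What to change.** In part A (Sample size selection):

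- For each endpoint, count candidate parameters, including every category level and nonlinear term, against the events in the data used for fitting.
- State that 100 fitting-set events correspond to 10 candidate parameters.
- Remove convergence as the criterion.

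In part C (Statistical Analysis):

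- Apply shrinkage or penalised estimation to the derived models, since 10 events per candidate does not by itself secure calibration.
- Report the calibration slope in the validation set alongside the Hosmer–Lemeshow test.

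The cost is wording and a standard analysis step on data already being collected. The downside is fewer candidates per endpoint, or shrunken coefficients that are slightly harder to turn into a point score.

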### Study goals and objectives

The purpose of this study is to clarify some of the previously stated questions and unknown factors. The specific study objectives are displayed in Fig. 1 and are: 1. To determine risk factors for death or major complications, reoperations, or readmissions in the short-term; 2. To determine risk factors for death, tumor recurrence, major complications, readmission or deterioration in quality of life in the mid-term; 3. to evaluate patient reported outcomes from before intervention to the end of the follow-up period. 4. To evaluate the role of biological markers in the prediction of adverse results; and 5. from a health services research perspective, to evaluate equity, appropriateness, access to care, treatment cost, and psychosocial support for patients.

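### The event count rests on one-year mortality and is not shown to carry over to the short-term death model of objective 1

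*Protocol article*

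**What the plan says.** The sample size subsection of the protocol article (Data management and statistical analysis, part A) asks for "at least 10 events of the dependent variable of interest" per independent variable in the logistic model, and derives from this that "at least 100 events of the dependent variable in the sample are required". The only rate it offers is mortality above 15% "of patients operated on in the first year, higher that the expected percentages of other parameters". It then states that over 300 events are expected for any of the dependent variables, without naming a time horizon.

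Objective 1 (Study goals and objectives) is "To determine risk factors for death or major complications, reoperations, or readmissions in the short-term". Objective 2 covers the mid-term. The Background gives 1 or 2 years as examples of medium-term follow-up. The Abstract lists the endpoints at 30 days and at 1, 2, 3 and 5 years. The section on hospital admission data says that "Data were subsequently collected up to 30 days after surgery", and the next collection runs through the first year.

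The Statistical Analysis text (part C) states that "Predictive models will be developed to address objectives 1 and 2". It gives death as one example of a binary outcome for hierarchical logistic models, after a random division into derivation and validation sets. It reads an AUC above 0.80 as good discrimination.

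**The concern.** The rate and the model have different horizons. A one-year death rate can support a one-year death model, which fits objective 2. It says nothing direct about how many patients die in the much shorter window of objective 1. The conclusion about 300 events is nevertheless worded to cover every outcome and carries no horizon, so a reader will take it to cover the short-term death model too.

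This is a question about death itself at an earlier time. It does not depend on the other outcomes being rarer than death, and it would remain if 15% were exactly right at one year.

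At stake is the reliability of a short-term mortality rule. The study collects the POSSUM variables in order to test those scores, and the Discussion promises simple prediction rules for short-term adverse events, death included. If 30-day deaths number in the tens, the plan's own rule allows only a handful of predictors, and the AUC criterion would be judged on few deaths.

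**Working it through.** **Inputs**
- Events per variable: 10; minimum events in the sample: 100; one-year mortality: above 15%, a lower bound (all from the sample size subsection).
- Sample: 2749 recruited (Table 1, Discussion). No planned sample size is stated.
- 30-day death rate: not given. Split fraction: not given.
- Short-term taken as 30 days: an inference from the data collection schedule and from the Background's use of medium-term.

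**1. The plan's own figure.** 300 / 0.15 = 2000 patients, and 0.15 × 2749 = 412 deaths. The statement of over 300 events is therefore consistent for one-year death.

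**2. What 30-day death would need.** This step needs no assumption about the shape of the hazard.
- For 100 deaths: 100 / 2749 = 3.6% 30-day mortality; 100 / 412 = 24% of first-year deaths.
- For 300 deaths: 300 / 2749 = 10.9%; 300 / 412 = 73% of first-year deaths.
- Because 15% is a lower bound, the shares fall if one-year mortality is higher. At 20% (550 deaths) they are 100 / 550 = 18% and 300 / 550 = 55%. At 25% (687 deaths) they are 15% and 44%. The required 30-day rates of 3.6% and 10.9% do not change.

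**3. Illustrative counts, each resting on an assumed hazard.**
- Constant hazard over the first year, 15% at one year: 1 − 0.85^(30/365) = 1.33%; × 2749 = about 36 deaths. With 20% or 25% at one year: 50 or 64.
- First-month hazard k times that constant rate: 1 − 0.85^(30k/365). For k = 2, about 72 deaths; for k = 3, 3.93% × 2749 = about 108.
- Weibull hazard falling over time, 15% at one year, shape 0.8, 0.7, 0.6 and 0.5: 60, 77, 98 and 125 deaths.

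**4. The derivation set, with assumed fractions of one half and two thirds.**
- Constant hazard: 18 and 24 deaths.
- Threefold first-month hazard: 54 and 72 deaths.
- 100 deaths in that set would need a 30-day mortality of 100 / 1374.5 = 7.3% or 100 / 1833 = 5.5%.

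**5. Consequence under the plan's own rule.** 36 deaths allow 3 to 4 predictors in the whole sample; 108 allow about 10. With 18 deaths among 1374 patients in a validation half, the Hanley–McNeil standard error at an AUC of 0.80 is 0.063, so the 95% half-width is 1.96 × 0.063 = 0.12. This last figure combines an assumed hazard with an assumed split and is only an illustration.

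**The case against.** A reader might infer that the 100-event minimum fails for 30-day death at the plan's own rate, with about 36 deaths. The article does not support that. It states no 30-day rate, 15% is a lower bound at another horizon, and 36 requires a constant hazard. Deaths after surgery may well cluster early, and a threefold first-month hazard already gives about 108, which meets the minimum in the whole sample. This objection stands, and the conclusion has to be conditional.

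The article also sets the minimum for the sample, not for the derivation set, and gives no split fraction. The derivation-set figures therefore show what is left for fitting the model; they do not show a breach of the stated rule. That stands as well.

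Objective 1 could be read as a composite of death, major complications, reoperations or readmissions, in which case deaths alone are not the event count. The wording allows this, but the Statistical Analysis text names death separately among the binary outcomes for objectives 1 and 2, so a death model is a natural reading.

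Overfitting follows only if the analysts use more predictors than their own rule permits, and predictor limits for each model may be set in a fuller document. That is fair. It does not rescue the article's statement about 300 events, which is made without a horizon and is not supported for short-term death.

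Finally, no arithmetic is wrong, and one year is a sensible planning horizon for objective 2. Both are true. The fault lies in extending the one-year figure to every outcome.

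**Conclusion.** The concern holds in a limited form. The one-year figure does not carry over to objective 1, and the article gives nothing else from which to judge the number of short-term deaths. For that model the 300-event statement is unsupported, and the 100-event minimum is not shown to be met. In the whole sample the minimum is missed unless 30-day mortality is at least 3.6%. Reaching 300 would take 10.9%, or nearly three quarters of first-year deaths in the first month if one-year mortality is 15%.

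These thresholds rest on the 2749 recruited patients and on reading short-term as 30 days; the shares also rest on 15% at one year. The actual count is unknown. The assumptions tried above span roughly 36 to 125 deaths in the whole sample, on both sides of 100.

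**What to change.** - Define short-term.
- Restrict the statement of over 300 events to one-year death.
- Give expected events by outcome and horizon, for the whole sample and for the derivation set, with the split fraction and the source of each rate.
- For 30-day death, cap the number of estimated parameters at observed deaths / 10. Alternatively, fit a penalised model on all patients and validate it internally by resampling instead of the random split.
- Report the AUC with its confidence interval.

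This changes the text of the sample size and analysis sections only; it needs no further patients or data. The downside is a more modest claim for the 30-day death model.
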